### Recruitment

Participants will be recruited over a 24-month period, or until the required sample size is achieved. A HF nurse will initially assess patients’ eligibility to participate in the study: those who meet the inclusion criteria will be referred to the study research assistant who will approach potential participants at their outpatient appointment, explain the study (both verbal and written information), and obtain their consent. They will be asked to identify if they have an informal carer or next-of-kin who would be willing and able to complete some questionnaires for the study. A research assistant will contact the carer, explain the study and their involvement, obtain consent and collect baseline questionnaires. Healthy control participants will be sourced from the community by advertisements in local newspapers and word-of-mouth. Research assistants will screen control participants for study eligibility, explain the study and obtain their consent to undergo the neurocognitive testing. Healthy control participants will be matched to HF patients according to age, premorbid intelligence and gender.

### Baseline and follow-up measures to be collected from all HF patient participants

A comprehensive baseline assessment of HF patients will be conducted prior to randomisation and the first intervention session. The baseline assessment will include socio-demographic, psychosocial, cognitive and clinical profiling using a combination of self-report and review of patient records. Table 1 displays baseline, 4-week and 12-month assessments. The following measures will be administered during the assessment:

**Table 1 Tab1:** **Assessment measures at baseline and post-intervention evaluations**

**Measures**	**Baseline**		
		**Assessment One** ^**b**^	**Assessment Two** ^**c**^
Physical functioning			
Physical examination (BP/HR/RR/weight/NYHA class, BNP)	X	X	X
Echocardiogram	X		X
‘Up and Go’ test	X	X	X
Timed Instrumental Activities of Daily Living (TIADL)	X	X	X
Unplanned readmission/survival		X	X
Self-care			
Heart-FaST	X		X
Patient engagement in self-care: (SCHFI and four consulting items from the EHFScBS)	X	X	X
Nurses and carer assessment of patient engagement in self-care	X	X	X
Review of patient symptom monitoring diary and how they perform self-care maintenance behaviours		X	X
Control Attitudes Scale - Revised (CAS-R)	X	X	X
Psychosocial functioning			
Quality of life (SF-12)^a^	X	X	X
Dyadic HF care typology	X		
Hospital Anxiety and Depression Scale (HADS)^a^	X	X	X
Cognitive functioning for HF patients			
Cognitive screen (MoCA)^a^	X	X	X
Assessment of PM (MIST, brief version of Virtual Week and naturalistic task)^a^	X	X	X
Working memory, executive functioning, verbal memory (CogState, N-Back, Trail Making Test)^a^	X	X	X
Premorbid intelligence (NART)^a^	X		
Caregiver			
Health screening questionnaire	X		
Caregiver (or next of kin) Contribution to Self-Care (CC-SCHFI)	X	X	X
Control Attitudes Scale - Revised (CAS-R)	X	X	X
Dyadic HF care typology	X		
Quality of life (SF-12)^a^	X	X	X
Modified Caregiver Strain Index (MCSI)	X	X	X
Proxy - IADL	X	X	X

Key: BNP, brain natriuretic peptide; BP, blood pressure; CC-SCHFI, Caregiver Contribution Self-Care Heart Failure Index; EHFScBS, European Heart Failure Self-care Behaviour Scale; Heart-FaST, Heart Failure Self-care Screening Tool; HF, heart failure; HR, heart rate; IADL, Instrumental Activities of Daily Living; MIST, Memory for Intentions Screening Test; MoCA, Montreal Cognitive Assessment; NYHA class, NART; National Adult Reading TestNew York Heart Association Classification; PM, prospective memory; RR, respiratory rate; SCHFI, Self-Care Heart Failure Index; SF-12, Short-Form 12-item health survey.

^a^Measures will also be collected from healthy non-HF controls at baseline; ^b^2 to 4 weeks post cognitive training; ^c^12 months post cognitive training.

I.*Patient clinical and socio-demographics*: age, gender, education level, social support, employment history. Patient clinical history, blood pathology (B-type natriuretic peptide (BNP), urea, electrolytes, full blood count), echocardiographic assessment of left ventricular systolic and diastolic function and assessment of valvular function, HF aetiology and treatments (medications, devices, surgery), physical examination (heart rate, blood pressure, respiratory rate, weight).II.*Heart Failure Screening Tool* (Heart-FaST) [36]: assesses three functional domains salient to patient engagement in self-care: physical, cognitive and emotional functioning. Higher scores on each barrier scale indicate worse functioning. Preliminary analyses support the construct validity of the Heart-FaST as a screening tool for physical, cognitive and emotional barriers that may hinder engagement in HF self-care. Heart-FaST, therefore, has the potential to assist clinicians in tailoring educational and surveillance disease management strategies to individual need [37].III.*Self-Care Heart-Failure Index* (SCHFI) [38]: assesses HF self-care behaviours and skills comprising 15 items rated on a 4-point scale to measure the process of self-care. There are three sub-scales: maintenance, management and confidence. Responses from each of the 3 self-care scales are transformed to a 100 point scale; higher scores reflect superior self-care. Self-care management scores are only computed for those patients reporting HF symptoms of ankle swelling or trouble breathing in the previous three months. Scaled scores > 70 are considered adequate self-care [38].IV.*European Heart Failure Self-care Behaviour Scale* (*EHFScBS*) [39,40]: 4 items from this scale will assess consulting behaviours in response to increased dyspnoea, feet swelling, weight gain and fatigue. Scores on the consulting subscale range from 4 to 20 with higher values indicating a lower likelihood of contacting providers for guidance when a change in signs or symptoms suggests worsening HF.V.*The Control Attitudes Scale - Revised* (CAS-R) [41]: assesses cardiac patients’ subjective perceived control in relation to managing their heart condition. Each of the 8 items is measured on a 5-point Likert scale ranging from 1 (strongly disagree) to 5 (strongly agree). Internal consistency in the HF population was Cronbach’s α = 0.76, and it showed good construct validity [41]. This scale will be administered to the HF patients, and will be adapted for administration to the caregivers. For example, one item on the CAS-R states: ‘If I do all the right things, I can successfully manage my heart condition’, and will be adapted for caregivers to state: ‘If I do all the right things, I can successfully manage the patient’s heart condition’. Similar amendments have been made in other studies investigating the perceived control of caregivers of patients with cardiac disorders [42,43].VI.*Short-Form 12-item health survey* (SF-12) [44]: assesses quality of life. The health survey consists of 12 items on a Likert response: 1) physical functioning, 2) physical role, 3) bodily pain, 4) general health, 5) vitality, 6) social functioning, 7) emotional role, and 8) mental health. Summary scale scores can be transformed to a scale of 0 to 10, with higher scores representing better health [44].VII.*The ‘Up and Go’ test* [45]: assesses functional mobility; stand from sitting, walk at usual speed for 3 meters, turn and return to sitting. To allow for test effect, an average of two timed trials will be recorded. The test is a measure of balance, walking ability and risk of falling in older populations and has been shown to be consistently reliable in test-retest analysis in patients with chronic conditions, including HF [45].VIII.*Dyadic HF care typology* [46,47]: describes the caregiving relationship between the HF patient and nominated carer. Both the HF participant and their carer will, independently, identify how their relationship functions in terms of managing HF symptoms. Care relationship types have been operationalised into: 1) caregiver responsible for the majority of the care of the HF patient, 2) HF patient responsible for the majority of their own care, 3) caregiver and the HF patient equally responsible for all aspects of the care, or 4) caregiver and the HF patient responsible for different aspects of the care.IX.*Hospital Anxiety and Depression Scale* (HADS) [48]: assesses anxiety and depression. Seven of the 14 items relate to anxiety and 7 relate to depression. Responses are provided on a Likert scale, and scores on each scale are interpreted in ranges: normal (0 to 7), mild (8 to 10), moderate (11 to 14), and severe (15 to 21). The 2 subscales have a mean correlation of 0.56, the mean Cronbach’s α is 0.83 for anxiety and 0.82 for depression [49].X.*Montreal Cognitive Assessment* (MoCA) [50]: screens for mild cognitive impairment in the domains of: visual-spatial skills; executive functions; language; attention; concentration; working memory; memory recall; and orientation. Low educational attainment is corrected by adding 1 point to the participant’s final score for ≤ 12 years of formal education. The highest possible score is 30 and a score 26 and above indicates normal cognitive function [50].

In a second interview, HF patients will undergo comprehensive PM and neurocognitive assessment, and TIADL, which will take 90 to 120 minutes to complete. The second interview will include the following:I.*Global cognitive screen*. The Addenbrooke’s Cognitive Examination Revised (ACE-R), a sensitive cognitive screening test of global cognitive functioning [35], measures 5 cognitive domains; attention/orientation, memory, verbal fluency, language and visuospatial abilities. Lower scores suggest poor cognitive performance. ACE-R is sensitive to early stages of dementia [51] and will be used as a participant screen. Adequate performance on the ACE-R is required for the participant’s data to be included in the final data sample.II.*Prospective memory* (*PM*). There will be a rigorous assessment of PM.The *Memory for Intentions Screening Test* (*MIST*) [52] is a standardised measure of PM developed for use in clinical settings. Throughout the test, participants will be required to remember and perform 4 time-based (for example; ‘in exactly 15 minutes please tell me it is time to take a break’) and 4 event-based tasks (for example: ‘when I hand you a red pen, please sign your name on the paper’). A series of word search puzzles will be provided as a distractor task to prevent overt rehearsal of the prescribed intentions. The researcher will monitor whether the participant remembers to perform the PM tasks correctly. Errors and scoring will be assessed in accordance with the MIST professional manual, which allows for an assessment of eight differing aspects of PM functioning. The MIST takes 30 minutes to administer. Total scores range from 0 to 48 with higher scores indicating better performance on the task. The MIST is sensitive to various neurological disorders, such as mild cognitive impairment [53] and has good reliability and validity [54].The brief *Virtual Week assessment*, which involves 2 ‘virtual’ days of the computerised board game, will assess event-based and time-based PM tasks. Based on our previous study with HF patients [55], the brief version of Virtual Week will take 30 to 45 minutes to complete.The *Naturalistic PM task* assesses 2 types of time-based PM tasks: 1) an appointment task at a set time of day and 2) one requiring monitoring a short interval of time. The latter is typical of many laboratory-based PM tasks. Participants will be asked to ring a prescribed number at 2 set times over 3 consecutive days. With each scheduled phone call, a recorded message will ask participants to call back after an interval of 5, 10 or 20 minutes.III.*Timed Instrumental Activities of Daily Living* (*TIADL*). Participants’ level of independence in daily activities will be assessed using a modified version of the TIADL [56]. Participants are required to complete nine activities that are relevant to tasks they would perform at home. The original five tasks are functional measures basic to independent living such as telephone communications, financial abilities, nutrition, shopping and medication use. Four additional tasks that are more relevant in the current technological communication environment and specifically related to HF self-care have been adapted for this study: 1) checking and sorting the sodium content of 3 food packages from the lowest to the highest amount of sodium; 2) extracting health information from a computer screen simulating a webpage to estimate a target heart rate for exercise; 3) extracting data from a webpage to look up a specified train timetable, and 4) finding a matching pair of black socks in a laundry basket full of mixed single socks. Participants are scored on the length of time to complete each of the nine activities, and if any, the type of error in performing the activity. Shorter completion times indicate better performance. The rapid and efficient completion of these tasks is advantageous in daily life and the time taken to complete the tasks is an objective indication of functional independence [56]. This assessment will be a key strength to the study, providing an objective and sensitive behavioural measure to evaluate the effectiveness of the cognitive training intervention on everyday functional independence.IV.*Working memory and executive functioning*. A battery of tests from the CogState program will be used (www.cogstate.com) [57,58]: i) The One Back Task assesses working memory. Participants are presented with a succession of playing cards on a screen and must decide if the card displayed is the same as the one presented immediately before; ii) The Two Back Task is presented in the same way as the One Back Task: however, participants are required to decide if the card displayed on screen is the same as a card presented two cards previously. Responses that are more accurate reflect better working memory, on both tasks; iii) The Detection Task measures psychomotor functioning and speed of processing. Participants must respond as quickly as possible to a card flipping over on screen, by pressing a button on the keyboard. Reaction time is measured and lower scores indicate better performance; iv) The Identification Task measures visual attention. Participants must decide whether a playing card presented on screen is red, by pressing the ‘Yes’ or ‘No’ button. Reaction time is measured and lower scores indicate better performance; v) The One Card Learning Task measures visual learning and memory. Participants are presented with a succession of playing card on screen, and must decide if the card currently displayed has been displayed previously. Accuracy of performance is measured, with higher scores indicating better performance. In addition to the computer battery of tests that take only 8 minutes to complete, there will be a pen and paper task, the Trail Making Test (TMT) [59], which assesses planning ability. It consists of two parts: Part A and B. In Part A, participants are required to draw lines to connect circles that are numbered consecutively; in Part B, participants connect circles that are numbered or lettered, alternating between the numeric and alphabetic sequences. This test takes approximately 5 minutes to complete, and the participant’s score is the total time taken to complete the task. Lower scores on the TMT indicate higher levels of planning ability.V.*Verbal memory*. In the Hopkins Verbal Learning Test-Revised [60,61], participants must listen to a list of 12 words read out by the experimenter, and then verbally recall as many words as possible from that list. This same procedure is repeated two more times. The participant is then asked, after a 20- to 25-minute interval, to verbally recall the same list of words. Following this final trial, the researcher reads out a list of 24 words and the participant is asked to identify the words that were presented in the original list of 12 words. This verbal memory test assesses episodic memory and the delayed recall test is particularly sensitive to ageing and abnormal ageing. The test has been successfully used in clinical and healthy populations of older adults [62].VI.*Premorbid intelligence*. The National Adult Reading Test (NART) [63] is a word-recognition test of vocabulary knowledge that requires participants to read aloud 50 English words of increasing difficulty that do not follow normal phonetic rules: for example, ‘chord’. This test takes about 5 minutes to complete and responses are audio-recorded for scoring purposes. The NART is widely used as an estimate of premorbid ability given the premise that reading ability is relatively independent of brain damage. Furthermore, NART performance appears to be impervious to the effects of many neurological and psychiatric conditions [64]. In a retrospective validity study of the NART, there was a strong correlation (*r* = 0.73; *P* < 0.001) between Intelligence Quotient (IQ) age 11 and NART performance at age 77 [64]. The NART will be used to characterise the HF sample and match the healthy non-HF controls on premorbid intelligence.

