
### Measures to be collected from healthy control group

The healthy control group will be matched to the HF patient group on age, premorbid intelligence and gender, and will undergo neuropsychological assessment as described above and highlighted with asterisks in Table 1. Psychosocial demographics, including social support and anxiety and depression, will also be collected to allow comparisons of the healthy controls and HF participants.

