### Statistical analyses

To compare and confirm cognitive deficits, including PM, between HF patients and a healthy matched control, group differences in baseline PM and neuropsychological tests will be examined using inferential statistics (*t*-test and analysis of variance; ANOVA). To analyse the changes in each measure assessed at each time point (baseline, Assessment One and Assessment Two) we will use separate mixed ANOVAs for all dependent variables. The within-groups variable will be *testing phase* (baseline, Assessment One, Assessment Two) and the between-groups variable will be *Training group* (PM training, word puzzles). Multiple regression analysis will be performed to identify whether physical, cognitive, emotional and mental functioning variables are independent predictors of HF self-care and consulting behaviours, after adjusting for clinical characteristics. For all analyses, α levels will be set at 0.05 and effects sizes will refer to partial η-square values.

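### In the HF versus healthy-control comparison, schooling is neither a named matching factor nor a covariate, and only the MoCA carries a described correction for it

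*Protocol article*

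**What the plan says.** All references are to the protocol article.

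- **Matching.** Recruitment: "Healthy control participants will be matched to HF patients according to age, premorbid intelligence and gender". The section on measures for the healthy control group gives the same three factors: "The healthy control group will be matched to the HF patient group on age, premorbid intelligence and gender". Education is in neither list. Controls are volunteers found through local press notices and personal contacts, while patients come from three hospitals.
- **How premorbid intelligence is measured.** Second interview, item VI: "The NART will be used to characterise the HF sample and match the healthy non-HF controls on premorbid intelligence". The NART "is a word-recognition test of vocabulary knowledge that requires participants to read aloud 50 English words of increasing difficulty".
- **MoCA scoring.** First interview, item X: "Low educational attainment is corrected by adding 1 point to the participant’s final score for ≤ 12 years of formal education". The next sentence fixes the range and cut-off: "The highest possible score is 30 and a score 26 and above indicates normal cognitive function".
- **Who takes the MoCA.** Table 1 marks it with footnote a: "Measures will also be collected from healthy non-HF controls at baseline".
- **Other tests.** The second-interview section describes no schooling correction for the MIST, Virtual Week, the naturalistic task, CogState, the Trail Making Test or the Hopkins test. MIST scoring is referred to its manual.
- **Analysis.** Statistical analyses: "group differences in baseline PM and neuropsychological tests will be examined using inferential statistics", namely t-test and ANOVA. Adjustment, for clinical characteristics, is named only for the separate regression on self-care.

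**The concern.** The MoCA rule acknowledges that years of schooling move a cognitive score. The comparison in which that matters most is the non-randomised one between hospital patients and self-selected volunteers, where the two groups may well differ in schooling. Yet schooling is absent from the matching list and from the named analysis. One test then has a one-point step at 12 years, and the others have only what NART matching removes indirectly.

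At stake is the first study aim, confirming cognitive and prospective memory deficits in HF. Part of an apparent deficit, or part of a difference between the MoCA and the memory tests, could reflect schooling and not HF.

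**Working it through.** **Yardstick from the plan.** The Sample size section speaks of 60 HF patients in this comparison, and the abstract gives 60 healthy controls. It claims power for moderate effects without a number. Taking moderate as 0.5 SD (assumption), two-sided 5% and 60 versus 60, power is 0.78 (normal approximation 0.782, noncentral t 0.775). There is no stated power, SD or schooling figure to reproduce.

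**Check 1: a schooling gap directly.** All three inputs are assumptions, because the documents give none:

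- g = share with 12 years or fewer among HF patients minus the share among controls, 0.1 to 0.3;
- b = raw MoCA points lost with low schooling, given age, gender and NART, 0 to 2;
- s = the same loss on another test, in SD units, 0 to 0.5.

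Bias (HF minus control):

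- raw MoCA: −g × b
- corrected MoCA: −g × b + g × 1 = g(1 − b)
- other test: −g × s

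At g = 0.2:

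| b | corrected MoCA bias (points) |
|---|---|
| 0 | +0.20 |
| 0.5 | +0.10 |
| 1 | 0 |
| 1.5 | −0.10 |
| 2 | −0.20 |

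| s | bias in another test (SD) |
|---|---|
| 0 | 0 |
| 0.2 | −0.04 |
| 0.5 | −0.10 |

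Over g = 0.1 to 0.3, the corrected MoCA bias runs from +0.3 to −0.3 points. With an assumed SD of 3 this is at most 0.3 / 3 = 0.10 SD in either direction. For the other tests the bias runs from 0 to −0.3 × 0.5 = −0.15 SD. With 60 versus 60 and no true difference, the two-sided rejection rate for such a test is 0.050 to 0.129.

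**Check 2: what NART matching may leave.** Matching on a proxy with validity r leaves (1 − r²) of a pre-existing ability gap. The second-interview section cites r = 0.73. I take 0.73 to 0.85, a gap of 5 to 10 IQ points between the source populations (SD 15), and a test–ability correlation of 0.3 to 0.5. All of these except 0.73 are assumptions.

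- Smallest: 5 × (1 − 0.85²) = 5 × 0.278 = 1.4 points; 1.4 / 15 × 0.3 = 0.03 SD
- Largest: 10 × (1 − 0.73²) = 10 × 0.467 = 4.7 points; 4.7 / 15 × 0.5 = 0.16 SD

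The noncentrality is d × √(60 × 60 / 120) = d × 5.48. The normal approximation gives two-sided rejection rates of 5.3% and 13.7%.

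The two checks rest on different models and reach nearly the same ceiling, 0.15 and 0.16 SD. That is about 30% of a 0.5 SD effect. The lower ends are negligible.

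**The case against.** **Matching on premorbid intelligence already covers every test.** This stands in part. NART score and schooling are related, so the match is an indirect control for schooling. It is not a match on years of education. How much it leaves is unknown: r = 0.73 links IQ at age 11 with NART at age 77 and includes decades of change and error in both tests, so a residual of 47% is an upper-end reading.

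**A covariate can be left to an analysis plan that is not shown.** This would settle the matter if the article were silent. It is not: it lists the matching factors twice, names the tests for this comparison, and reserves adjustment for another aim. The point is an improvement on a stated method, not a complaint about missing detail. The one-point MoCA rule is presented as part of the instrument's scoring and is not an error.

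**Stronger readings that the documents do not support.**

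- A reader might infer that a schooling gap must push the MoCA and the memory tests in opposite directions. If HF patients are the less schooled group, this happens only if b < 1 and s > 0. At b = 1 the corrected MoCA is unbiased, and above 1 it is biased the same way as the other tests.
- A reader might link this to the planned paper on prospective memory as a missing link. Its full title concerns engagement in self-care, which belongs to the regression aim and not to this comparison.
- Check 2 might be read as the effect of schooling. It measures residual ability confounding, of which adjustment for education removes an unknown part.

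**Conclusion.** The point holds in a modest form. Schooling is not a named matching factor or covariate in the HF versus healthy-control comparison, and only the MoCA has a described correction, so a remaining schooling gap can bias the results and is treated unequally across tests. Neither the sign nor the size can be established from the documents. Under the assumptions shown, the bias is about 0 to 0.16 SD, and the false-positive rate per test about 5% to 14% with 60 versus 60. That rate counts errors in both directions, so its base is 5%. The 60 versus 60 basis follows the Sample size section; using all 200 patients would be a different comparison from the one sized there.

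This concerns a baseline, non-randomised aim. The comparison of the two training groups is untouched. It is a cheap improvement and not a flaw that threatens the trial.

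**What to change.** In Statistical analyses, for the HF versus healthy-control comparison only:

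1. Replace the unadjusted t-test and ANOVA with ANCOVA or regression that includes education, age, gender and NART, for every cognitive and prospective memory score.
2. Enter education as years if recorded in both groups, otherwise as the split at 12 years that MoCA scoring already requires.
3. Use the uncorrected MoCA total in these models, so that schooling is not corrected twice. With years as the covariate the choice matters. With the 12-year split it changes the group estimate only through the ceiling of 30, because the bonus is itself that split.
4. Keep the corrected total for classification against the cut-off of 26.

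**Cost.** Four covariates take the residual degrees of freedom from 118 to 114 with 60 versus 60. Education level is listed for HF patients, but the section on controls does not name it, and the MoCA rule needs only a yes or no at 12 years. Recording of years for controls should therefore be confirmed. Adjustment will remove the schooling part of the bias but not every difference between hospital patients and volunteers.
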